### Assessments and outcomes

The primary aims of this study are to evaluate the efficacy of the DANE Recovery Model to improve the cognitive recovery of older emergency surgery delirium survivors, as determined by the Repeatable Assessment of Neuropsychological Status (RBANS). Secondary aims include evaluation of physical and psychological recovery, as measured by the Short Physical Performance Battery, Medical Outcomes Study Short Form (SF-36), Patient Health Questionnare-9 (PHQ-9), and Generalized Anxiety Disorder Scale (GAD-7).

### Data collection

Chart review will be used to abstract relevant covariables. Baseline assessments will occur at or as close (within 4 weeks) to hospital discharge as possible. After baseline assessments, outcomes will be collected at 6, 12, and 18 months. We will make every effort to retain patients during the 18-month study period and complete all follow-up instruments. We will attempt to do this in person. We will abstract data in a standardized fashion into a REDCap database. We will ensure data quality by independent abstraction and double data entry of 10% by the site PI or suitable designee. Any changes to the study protocol, including those related to the inclusion and exclusion criteria, will be communicated to key personnel, trial participants, program officers, and IRBs.

### Description of study instruments

#### Repeatable Battery for the Assessment of Neuropsychological Status (RBANS) [14]

This is a commonly used battery for cognitive function. Originally developed as a screening instrument for older adults with suspected dementia, it is now used in a wider age range and a variety of neuropsychological problems. This instrument is comprised of twelve subtests that aggregate to a total and index score across five domains: immediate memory, visuospatial-constructional, language, attention, and delayed memory. Index scores are then converted to age-based standard scores (M = 100, SD = 15). The test is versatile with four equivalent forms to allow for serial assessment. It takes approximately 30 min to administer.

#### SF-36 [15, 16]

This widely validated and used study instrument evaluates eight components of quality of life: physical functioning, role physical, bodily pain, general health, vitality, social functioning, role-emotional, and mental health. These components are aggregated into a physical component summary (PCS) and a mental component summary (MCS). Differences of more than two points are considered clinically significant for both component summary scores.

#### PHQ-9 [17] and GAD-7 [18]

The former is a depression scale that consists of nine items with a total score of 0–27, and the latter is an anxiety scale that consists of seven items. These instruments are also widely validated with good internal consistency and reliability for the diagnosis of major depression and generalized anxiety disorder. A change of two points is considered clinically significant.

### Statistical analysis

We will compare randomization results to the planned randomization schedule. Baseline characteristics between the intervention and standard care arm will be compared using analysis of covariance (ANCOVA) for continuous variables and the Cochran-Mantel-Hansel statistic for categorical variables while adjusting for stratifying variables. Patients will be stratified by hospital and surgery (vascular vs. non-vascular procedures). We will also examine the distributions of continuous variables in order to verify the normal distribution assumption, and use alternative procedures (transformation or non-parametric methods) if this assumption is violated. Frequency distributions of all categorical variables will also be examined, and exact inference procedures will be used in cases of zero or small cell size. Intention-to-treat analysis will be conducted for the primary and secondary aims.

For our primary outcome of cognitive recovery, we will use mixed effects models with repeated RBANS scores collected at baseline and at 6, 12, and 18 months as outcome measures. Group, time, a group-by-time interaction, and other baseline covariates found to be significantly different in univariate comparisons will be used as independent variables. We will adjust for stratification variables. We will also conduct post hoc comparisons at each follow-up time following a significant interaction between group and time to determine the time when a group difference can be detected. Parameter estimation and inference for the mixed-effects models are conducted using the maximum likelihood approach which are robust under many missing data mechanisms.

For our secondary aims of physical and psychological recovery, we will develop separate mixed effects models for physical function scores (SPPB and physical component score on the SF-36) collected at baseline and at 6, 12, and 18 months as the outcome measures for the former and PHQ-9, GAD-7, or mental component score on the SF-36 for the latter. In both sets of models, we will use the same independent variable selection and stratification variables as in our primary outcome.

In an exploratory analysis, we will plan to investigate the heterogeneity of treatment effects whenever a treatment effect is detected in order to determine if the treatment has different effects in various subgroups defined by sex, race/ethnicity, socioeconomic status, and age.

We completed a sample size calculation using a mixed effects model and adjusted for correlations among repeated measures. Effect sizes were derived from prior work [9, 12, 19, 20]. Assuming a base correlation of 0.3 and a decay rate of 0.1 in a linear exponent autoregressive correlation structure for repeated measures and effect sizes of 0.2 SD at 6 months, 0.4 SD at 12 months, and a maintained effect size of 0.4 SD at 18 months, 185 participants per group are required to yield a power of 80.6% to detect differences in the change in RBANS between the intervention and usual care groups with type I error rate at *α* = 0.05. Assuming a 30% attrition rate, we need to enroll 264 patients per group into the study with a total enrollment target size of 528. Similar power will be achieved for the secondary outcome measures. Power estimates were calculated using the GLMPower procedure in SAS 9.4.

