## Methods and design

### Study population (Tables 1 and 2)

**Table 1 Tab1:** Study timeline

	Year 1				Year 2				Year 3				Year 4				Year 5			
	1	2	3	4	1	2	3	4	1	2	3	4	1	2	3	4	1	2	3	4
Start-up (hire/train staff, make study manuals, create data entry system)	X	X																		
Enrollment and randomization		X	X	X	X	X	X	X	X	X	X									
Deliver interventions			X	X	X	X	X	X	X	X	X	X	X	X	X					
Outcome measures			X	X	X	X	X	X	X	X	X	X	X	X	X	X	X	X	X	
Data entry and management			X	X	X	X	X	X	X	X	X	X	X	X	X	X	X	X	X	
Analyze data and submit report to DSMB				X	X	X	X	X	X	X	X	X	X	X	X	X	X	X	X	X
Present results at national meetings																		X	X	X

**Table 2 Tab2:** Schedule of activities

	Screening, day 14–0	Enrollment/baseline, day 0	Acute stage, months 0–1	Recovery state, months 2–6	6-month follow-up, weeks 21–31	Maintenance stage, months 7–12	12-month follow-up, weeks 47–57	18-month follow-up, weeks 73 to 91
RA screens for eligibility and development of delirium	X							
Daily delirium assessment: RASS and CAM-ICU-7^a^	_X_ ^a^							
DAST-10^a^	_X_ ^a^							
Informed consent	X							
Demographics		X						
Behavior checklist		_X_ ^b^			X		X	X
RBANS		_X_ ^b^			X		X	X
TMTs A and B		_X_ ^b^			X		X	X
SCWT		_X_ ^b^			X		X	X
IUTT		_X_ ^b^			X		X	X
SPPB		_X_ ^b^			X		X	X
SF-36		_X_ ^b^			X		X	X
GAD-7		_X_ ^b^			X		X	X
PHQ-9		_X_ ^b^			X		X	X
Delirium Experience Questionnaire		_X_ ^b^						
Lawton-Brody IADL		_X_ ^b^						
Katz ADL		_X_ ^b^						
QDRS		_X_ ^b^						
Randomization^c^		_X_ ^c^						
Medical history		X						
AE review and evaluation		X	X	X	X	X	X	X
Initial case review^d^			_X_ ^d^					
First virtual visit with CC^d^			_X_ ^d^					
Development of recovery care plan^d^			_X_ ^d^					
Second virtual visit with CC^d^			_X_ ^d^					
Interaction period^d^			_X_ ^d^	_X_ ^d^	_X_ ^d^	_X_ ^d^		

^a^RASS, CAM-ICU-7, and DAST-10 performed as needed during screening to confirm eligibility. RA may perform CAM-ICU-7 up to twice daily

^b^RA will obtain baseline measurements *ideally* within 48 h of anticipated hospital discharge *or* up to 4 weeks after discharge

^c^Randomization to occur *after* screening, consent, and completion of baseline assessments, *ideally* within 48 h of anticipated hospital discharge *or* up to 4 weeks

^d^EGS delirium recovery model only

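### The primary RBANS model gives each arm its own pre-randomization baseline mean; the test is valid but inefficient, and a common baseline would cut its standard errors by about 19-26% at the planning correlations

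*Protocol article*

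**What the plan says.** The Statistical analysis section of the protocol article sets the outcome vector: "we will use mixed effects models with repeated RBANS scores collected at baseline and at 6, 12, and 18 months as outcome measures". The terms are fixed in the next sentence: "Group, time, a group-by-time interaction, and other baseline covariates found to be significantly different in univariate comparisons will be used as independent variables". Nothing there restricts the arms to a common mean at baseline, and baseline RBANS is an outcome, not a covariate. Follow-up testing is conditional: "We will also conduct post hoc comparisons at each follow-up time following a significant interaction between group and time". The secondary outcomes (SPPB, SF-36 component scores, PHQ-9, GAD-7) also get mixed models with baseline among the outcomes and the same choice of independent variables.

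The sample size paragraph sets its target as the between-arm difference in RBANS change. Its inputs are "Assuming a base correlation of 0.3 and a decay rate of 0.1 in a linear exponent autoregressive correlation structure" and "effect sizes of 0.2 SD at 6 months, 0.4 SD at 12 months, and a maintained effect size of 0.4 SD at 18 months", leading to "185 participants per group are required to yield a power of 80.6" per cent.

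Footnote c of Table 2 places randomization after "screening, consent, and completion of baseline assessments", and the Randomization and blinding section gives the same order.

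**The concern.** With baseline among the outcomes and a free group term, the model estimates a baseline difference that randomization has already set to zero in expectation. The interaction then measures each follow-up difference net of the observed baseline difference. This amounts to adjusting for baseline with the slope fixed at 1. If baseline and follow-up correlate weakly, as the plan assumes, the best slope is far below 1 and the subtraction adds variance. At a correlation of 0.3, a change score has variance 1.4 (in units of the outcome variance), against 1.0 if baseline were ignored and 0.91 with proper adjustment.

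What is at stake is precision and power on the primary outcome and on each secondary outcome analysed the same way, in a trial of 528 patients.

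**Working it through.** **Inputs.** From the sample size paragraph: n = 185 per group; group differences 0, 0.2, 0.4, 0.4 SD at 0, 6, 12, 18 months; base correlation 0.3 and decay 0.1; alpha 0.05. From the statistical model: free baseline, so the interaction has 3 df.

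**Step 1: reproduce 80.6%.** Write ρj for the correlation of baseline with visit j. The change contrasts have covariance S with diagonal 2(1 − ρj) and off-diagonal 1 − ρj − ρk + ρjk. Let e = (0.2, 0.4, 0.4). The noncentrality is λ = (n/2) e′S⁻¹e, referred to a noncentral F with 3 and 2n − 4 = 366 df.

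- Correlations 0.3/0.2/0.1 by lag: S has diagonal 1.4, 1.6, 1.8 and off-diagonals 0.8 (6 and 12 months), 0.8 (6 and 18), 1.0 (12 and 18). Then λ = 11.17 and power = 80.6%, which matches the stated figure at n = 185.
- Usual exponent form, 0.30/0.28/0.27: λ = 13.80 and power = 88.8%. This form would need only about 150 per group for 80.6%.

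The stated power is therefore that of the free-baseline change test, apparently with correlations falling by 0.1 per visit. The article does not list the correlations, so this is an inference from the match.

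**Step 2: common baseline.** Each follow-up contrast now has variance 1 − ρj² in place of 2(1 − ρj). The ratio of standard errors is √[(1 − ρj²) / 2(1 − ρj)] = √[(1 + ρj)/2]. In SD units, SE = √(2/185 × variance).

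| Correlations 0.3/0.2/0.1 | 6 mo | 12 mo | 18 mo |
|---|---|---|---|
| 2(1 − ρ) | 1.40 | 1.60 | 1.80 |
| 1 − ρ² | 0.91 | 0.96 | 0.99 |
| SE, free baseline | 0.1230 | 0.1315 | 0.1395 |
| SE, common baseline | 0.0992 | 0.1019 | 0.1035 |
| Ratio | 0.81 | 0.77 | 0.74 |

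For the joint test, the covariance given baseline has off-diagonals ρjk − ρjρk = 0.24, 0.17, 0.28. Then λ = 24.11 and power = 99.1%.

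Under the exponent form the ratios are 0.81/0.80/0.80, λ rises from 13.80 to 26.08, and power from 88.8% to 99.5%.

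**Step 3: dropout.** Assume 264 per group with monotone loss to 185 completers, spread about evenly over the visits (the protocol gives only the 30% total). The SE reductions are then 18-21% with 0.3/0.2/0.1 and 16-18% with the exponent form.

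**Step 4: sensitivity to the correlation (assumed values, complete data).** The SE reduction is 1 − √[(1 + ρ)/2]: 26% at 0.1, 19% at 0.3, 13% at 0.5, 8% at 0.7, 5% at 0.8. With all correlations equal to 0.7 and the stated effects, the planned test already has 99.9% power, so the gain there is precision only.

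**Step 5: visit-wise comparisons.** If these are plain group differences at a visit, the free-baseline SE with complete data is √(2/185) = 0.1040 and the ratio is √(1 − ρj²). That is 0.954/0.980/0.995 with 0.3/0.2/0.1 and 0.954/0.959/0.964 with the exponent form, a reduction of about 0.5-5%.

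**Step 6: the gate.** A simulation of the 3-df interaction test followed by unadjusted 5% comparisons gives these family-wise error rates over the null visits: about 9% if a 0.4 SD effect exists at one visit only, about 5% or less if at most one visit is null, and 3-4% under the global null.

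**The case against.** The strongest reply is that nothing here is wrong. The group-by-time test is unbiased and keeps its type I error, the trial was sized for a difference in change, and the stated power reproduces on that basis. Plan and power agree. All of this stands: the point is a precision gain, not an error in the document.

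The second reply is that a gain of around 20% depends on a planning correlation that may be too low for a repeated cognitive battery. This also stands. The protocol reports no observed correlation, and at 0.7-0.8 the gain is 5-8%.

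A reader might go further in four ways, none of which the protocol supports:

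- *Baseline information is thrown away.* It is used, but with the slope fixed at 1 in place of an estimated one.
- *Every visit-wise comparison would be about 20% more precise.* The wording, comparisons at each follow-up time, reads most naturally as plain group differences at that visit. At the planning correlations those gain only 0.5-5%.
- *The plan starts from 89% power.* That is the exponent-form reading; the stated figure is 80.6%.
- *The visit-wise tests run at 9% error.* That needs a real effect at exactly one visit and none at the other two. The planned pattern of 0.2, 0.4 and 0.4 SD has no null visit. The comparisons are also labelled post hoc, and their adjustment may be left to an analysis plan not shown here.

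**Conclusion.** The point holds as a recommended improvement. The planned primary test is valid but less precise than the same data allow, because it estimates a baseline difference known to be zero by design. At the correlations that reproduce the stated power, the change contrasts would have standard errors 19-26% smaller and the 3-df test would move from 80.6% to about 99% power. Under the exponent-form reading the figures are 19-20% and 88.8% to 99.5%.

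These sizes rest on a baseline-to-follow-up correlation near or below 0.3, the stated effect sizes and complete data on 185 per group. The direction does not: the standard error of the change contrasts falls at any correlation below 1. The equal-means constraint adds no assumption beyond randomization after the baseline assessment, which the protocol specifies.

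The multiplicity point is secondary and does not change this conclusion.

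**What to change.** Before unblinding, specify one of two models for RBANS:

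- keep all four time points as outcomes but constrain the arms to one baseline mean (no group effect at time 0); or
- use 6, 12 and 18 months as outcomes, with baseline RBANS as a covariate interacting with time.

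In either case make the primary test the joint 3-df test of the group effects at 6, 12 and 18 months. In the second model this must include the group main effect, since the interaction alone would test only whether the effect differs between follow-up visits. Apply the same model to SPPB, the SF-36 component scores, PHQ-9 and GAD-7. State the correlation matrix behind the 80.6%, since the two readings of the structure give different power.

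Optionally, report the visit-wise comparisons with Holm-adjusted p-values, and say whether they are plain differences or differences in change.

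The cost of the model change is a line of code and revised wording; it needs no extra patients, visits or data. The Holm step makes visit-wise p-values slightly less favourable.

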### Randomization and blinding

On or within 48 h of anticipated hospital discharge and after obtaining informed consent, the RA will obtain baseline measurements of physical function, depression, anxiety, quality of life, and cognitive ability. Subjects will then be randomized in a 1:1 manner via a computer-generated randomization scheme, stratified by recruitment site and surgery type (vascular or non-vascular surgery). All subjects will receive the interventions described under usual care. We will make every effort to blind the research staff performing the assessments to the intervention group. Intervention allocation will be coordinated centrally through the University of Wisconsin to minimize staff exposure to randomization assignments. Furthermore, the study staff will adhere to a strict study script during survey administration with patients and caregivers, and a standardized chart abstraction protocol with a data dictionary will be used. Due to the type of intervention, blinding of the patients is not possible. Physicians and other providers caring for the patient will be made aware of the study but not its objectives. Though collaborative care adverse event rates are low, blinded adverse event rates will be presented to the statistician and principal investigators throughout the trial. Decisions regarding unblinding will be made if there are elevated adverse event rates. The research team will be unblinded should any serious adverse events be deemed to be related to the intervention and the DSMB notified immediately.

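### As the model terms are listed, adjusting for stratification variables and covariates has almost no effect on the group-by-time test that decides the primary outcome

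*Protocol article*

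**What the plan says.** All references are to the Statistical analysis section of the protocol article unless stated otherwise.

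- **Outcomes.** The primary analysis uses "mixed effects models with repeated RBANS scores collected at baseline and at 6, 12, and 18 months as outcome measures". Baseline RBANS is therefore part of the outcome vector and not a covariate.
- **Terms.** "Group, time, a group-by-time interaction, and other baseline covariates found to be significantly different in univariate comparisons will be used as independent variables". A separate sentence adds "We will adjust for stratification variables". No interaction with time is named other than group-by-time.
- **Deciding test.** Visit-wise results come second, as "post hoc comparisons at each follow-up time following a significant interaction between group and time". The sample size paragraph powers the trial "to detect differences in the change in RBANS between the intervention and usual care groups". Both make the difference in change the deciding comparison.
- **Secondary outcomes.** "In both sets of models, we will use the same independent variable selection and stratification variables as in our primary outcome".
- **Strata.** The Randomization and blinding section stratifies by recruitment site and by vascular versus non-vascular surgery. There are eight hospitals.

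**The concern.** A covariate that enters as a main effect adds the same amount to a patient's expected RBANS at baseline, 6, 12 and 18 months. Any change from baseline subtracts that amount out again. If the deciding comparison is a difference in change, a main-effect adjustment has nothing to act on, whatever covariates are chosen.

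Three things are at stake.

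- **Precision.** Variation in recovery between hospitals, surgery types or prognostic groups stays in the error term of the test.
- **Calibration.** Randomising within strata and then testing as if there were none makes standard errors slightly too large, so the test is conservative.
- **Imbalance.** The plan picks covariates because the arms differ on them, evidently to remove that difference. If such a covariate influences recovery as well as level, a main effect leaves its influence on change in the treatment estimate.

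The secondary models inherit the same structure.

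**Working it through.** **1. Reproducing the plan's power.** Inputs from the article: 185 per group; effects of 0.2, 0.4 and 0.4 SD at 6, 12 and 18 months; alpha 0.05; "Assuming a base correlation of 0.3 and a decay rate of 0.1 in a linear exponent autoregressive correlation structure". I took the baseline effect as 0 and the correlations as 0.3, 0.2 and 0.1 at one, two and three visits apart. This reading reproduces the stated figure.

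For the changes from baseline, c = (0.2, 0.4, 0.4). Their covariance matrix V has variances 1.4, 1.6 and 1.8 and covariances 0.8, 0.8 and 1.0.

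- c'V⁻¹c = 0.12074
- Noncentrality = (185/2) × 0.12074 = 11.17
- Noncentral F with 3 and 366 df: power 80.6%, as stated

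The powered test is therefore the 3-df group-by-time test.

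**2. Why main effects drop out.** Let a patient's four scores Y have covariance S, and let C hold the three change contrasts, whose rows each sum to zero. Then Cov(1'S⁻¹Y, CY) = 1'S⁻¹SC' = 1'C' = 0. The weighted mean and the changes are uncorrelated. A time-constant term affects only the weighted mean. Because the group main effect is free, group-by-time is estimated only from the changes.

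**3. Complete data, by simulation.** Maximum likelihood fits used 370 patients, eight sites, surgery type and one imbalanced covariate.

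- Random intercept: the interaction estimates were 0.131904, 0.375306 and 0.445079, each with SE 0.123521, both with and without the main effects. Only the baseline group difference moved, from −0.249 to −0.126.
- Unstructured covariance: estimates, SEs and the 3-df Wald statistic were identical to every printed digit. Covariate-by-visit terms moved the estimates by 0.011 to 0.012 SD on average when the covariate did not affect trajectory, and by 0.024 to 0.044 SD when it did.

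**4. About 30% dropout, 528 patients, unstructured covariance.** Main effects moved the estimates by 0.010 to 0.016 SD on average and cut SEs by about 1 to 2%. Mean Wald statistics were:

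| Covariate affects trajectory | No covariates | Main effects | By-visit terms |
|---|---|---|---|
| No | 20.30 | 20.80 | 20.84 |
| Yes (assumed) | 17.39 | 17.62 | 20.73 |

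In the second row main effects recover (17.62 − 17.39)/(20.73 − 17.39) = 0.23/3.34, or about 7% of the available gain.

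**5. Precision and conservatism.** The article gives no share R² of the variance of change explained by strata and covariates, so these are assumed values. Power uses noncentrality 11.17/(1 − R²). The error rate uses P(χ²₃ > 7.815/(1 − R²)) and applies if the balanced strata alone explain that share.

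| R² | Power with effective adjustment | True error rate without it |
|---|---|---|
| 0 | 80.6% | 5.0% |
| 2% | 81.4% | 4.7% |
| 5% | 82.8% | 4.2% |
| 10% | 84.9% | 3.4% |

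**6. Imbalance.** At 264 per arm, a difference just significant at 0.05 is 1.96 × √(2/264) = 0.17 SD. The bias left in the change is 0.17 × (follow-up slope − baseline slope). With an assumed follow-up slope of 0.3:

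| Baseline slope | Bias left |
|---|---|
| 0 | 0.051 SD |
| 0.1 | 0.034 SD |
| 0.2 | 0.017 SD |
| 0.3 | 0 |

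For the first row, 400 simulated trials with 30% monotone attrition gave an 18-month bias of 0.052 SD unadjusted, 0.051 SD with main effects and 0.002 SD with by-visit terms.

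**The case against.** The strongest reply is that the article never says the terms enter only as main effects. It promises adjustment without giving its form, and model detail of this kind often sits in an analysis plan that is not shown. It is true that main effects are the natural reading and not stated text. The point still stands, because the article does print a term list and names one interaction. Followed as written, that list makes the promised adjustment nearly empty for the deciding test.

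Four further objections narrow the claim.

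- **Exactness.** Exact cancellation needs complete data and, for standard errors, a suitable covariance structure. Under a fitted AR(1) structure with complete data, the estimates did not move but the 18-month SE fell 3 to 4%, with the Wald statistic going, for example, from 14.62 to 15.53. The article does not fix the structure for analysis.
- **Post hoc comparisons.** If these are group differences at a visit, they do receive the main-effect adjustment. An essentially unadjusted gate would then be followed by adjusted estimates.
- **Equal influence.** A covariate acting equally at every visit is already removed by the change contrast, so it needs no adjustment there.
- **Assumed sizes.** Neither the explained variance nor the slopes come from the article.

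A reader might infer that the primary test is invalid, biased or underpowered. The document does not support that. Under 1:1 randomisation the expected imbalance is zero, ignoring strata makes the test conservative, not liberal, and the stated 80.6% is reproduced without any help from covariates.

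**Conclusion.** The concern holds in a limited form. On the natural reading of the printed terms, adjustment for site, surgery type and covariates does nothing to the group-by-time estimates with complete data and very little under the planned attrition. Validity and sample size are not in question.

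The loss is modest. If 2 to 10% of the variance of change is explained, about 1 to 4 percentage points of power are forgone; if balanced strata alone explain that share, the true error rate is about 4.7% to 3.4%. The one threat to the estimate is a chance imbalance in a covariate that affects change. At 0.17 SD imbalance this leaves between 0 and 0.05 SD, at most about 13% of the planned 0.4 SD (0.051/0.4). The upper end requires a covariate that is unrelated to baseline RBANS and has a slope of 0.3 on follow-up RBANS.

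**What to change.** In the primary RBANS model and in all secondary models, enter surgery type, site and each adjustment covariate together with its interaction with visit. Report the group-by-visit effects from that model as the treatment effects. If by-visit terms are already intended, saying so settles the point.

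The change is one of wording and needs no new data. Stratum-by-visit terms cost up to 7 × 3 + 1 × 3 = 24 parameters, against 370 × 3 = 1,110 follow-up scores from 185 completers per arm. Each further single-parameter covariate adds three. Site-by-visit cells may be sparse, so small hospitals may need pooling, under a rule fixed before unblinding.
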